**Methods/Design:**

A multi-centre, randomized, two-group parallel group trial design will be adopted. Two hundred healthcare employees will be randomly assigned to one of two educational interventions: Beyond Silence, a peer-led program customized to the healthcare workplace, and Mental Health First Aid, a standardized literacy based training program. Pre, post and 3-month follow-up surveys will track changes in knowledge (mental health literacy), attitudes towards mental illness, and help-seeking/help-outreach behavior. An intent-to-treat, repeated measures analysis will be conducted to compare changes in the two groups over time in terms of the primary outcome of behavior change. Linear regression modeling will be used to explore the extent to which knowledge, and attitudes predict behavior change. Qualitative interviews with participants and leaders will also be conducted to examine process and implementation of the programs.

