The plan is to enroll 200 employees in total, with 100 participants in each group. In each of the four intake periods, we plan to include 24 to 26 participants, and will actively recruit to ensure sufficient numbers prior to randomization. Following randomization, an intent-to-treat analysis will be incorporated, including all study participants. Quantitative precision estimates suggest that this sample size is sufficient to detect any real and important benefit of CBE over literacy training on change in help-seeking behavior. Two RCT evaluations of MHFA (literacy) interventions among Australian healthcare workers found that 50% to 75% of workers reportedly offered help to a person with mental health problems, prior to the intervention [24,25]. Based on this, we expect an average of about 1–2 behaviors at baseline across the samples. To simplify, we approximate the precision to detect change in mean count from baseline to the 6 month follow-up using calculations for the linear mixed-effects model, but allowing for non-constant variance of the counts by assuming that the variance averaged over groups and occasions might be as high as 4. Also assuming high consistency of help-seeking within groups (test-retest correlation, 0.80), we have an 80% chance of finding a significant (p < .05) difference between the two groups in average change over 6 months of as little as 0.44 behaviors. That is, even if the real advantage of CBE over MHFA is very small (less than 1 new behavior, on average), we have a high probability of detecting it. The precision for estimating mediators such as changes in stigma scores is similarly high. Based on initial pilot data, there were significant increases in behavior over time therefore the projected sample size should be more than sufficient to detect change.

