The survey will include 6 main sections. Content and data collection methods will be identical in the two groups:**Demographic data** (gender, age, education, ethnicity, job tenure, position) will be gathered to obtain a basic profile of participants.**Mental health experience** – Participants will be asked whether they have a history of mental health issues, either in themselves or a family member (yes/no), the nature of these issues (examples provided), and any personal experiences with mental health issues over the past six months (yes/no). The presence of mental health issues is based on self report, and will be defined as changes in thinking, mood or behavior that impair day-to-day functioning [34]. This lay definition and examples will be provided to capture a range of experiences that may or may not have been formally diagnosed by a medical practitioner.**Help-seeking behavior** – Participants will be asked to report whether they accessed any services from a list of 10 health, workplace and community service options. Questions regarding service utilization are adapted from the 2012/2012 Canadian Community Health survey [36], in order to provide a population reference, although several work-related services (e.g. EAP, union) are added as an option. Participants may endorse more than one of the behaviors, and a summative score of the number of behaviors will be used to measure change in help-seeking. Since the incidence of reported help seeking may be low over the time frame of the study, attitudes or intent to seek help will also be tracked. Intention to seek psychiatric help is a significant predictor of behavior [18]. The Attitudes Toward Seeking Professional Psychological Help Scale–short form (ATSPPHS), a 10 question survey using a four point Likert-type scale response will be used to track beliefs and intent to seek professional help [37]. It is a widely used scale with good internal consistency (α = .78), and criterion validity supported by links between scale scores and mental healthcare use [37].**Outreach behavior** – Baseline and follow-up data will be gathered regarding personal contact with a co-worker about mental health problems (yes/no), and any contact over the past 6 months (yes/no). If contact did occur, participants will be asked whether they provided help to the co-worker, and if so, to identify the type of help from a list of 10 possible options. The list of “outreach” behaviors was based on the ones used for evaluation of the MHFA program (e.g. ‘spent time listening to problem’, ‘recommend professional help’) [34], with an adaptation to include a several work-specific options (e.g., ‘recommend EAP’, ‘offered assistance with job duties’). Participants are invited to check all behaviors that apply (with an open-ended option), and scoring is based on one point per action, with a summative score used to track change. In addition to the behavior list, participants will be asked to rate their confidence in providing help on a 7-point Likert scale.**Stigma towards co-workers with mental illness** – The MHCC Opening Minds Scale for Healthcare Providers will be used; a 20-item questionnaire that was designed to evaluate the attitudes of healthcare providers towards people with mental illness [38]. The tool has good internal consistency (α = .82), and satisfactory test-retest reliability (ICC = .66), with limited impact of social desirability [38]. This tool is being implemented in sites across the country by researchers with the Mental Health Commission Opening Minds team; therefore data from this project can be linked with the larger database.**Mental Health literacy** – Four vignettes of employees with workplace mental health issues will be used to assess awareness of issues and when/how to respond to these issues in the workplace. The vignettes are adapted for a healthcare workplace based on a review of vignettes reported in the literature study [33,39,40], as well as analysis of key issues reported in the pilot phase of the study. Vignettes will incorporate differences in gender, nature and severity of illness, and a 7-point Likert scale from novice to expert will be used to track key dimensions of literacy, including perceived knowledge about the condition, what to say/do and what resources to access [33].

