### Data analysis

In accordance with Research Question 1, we hypothesize that help-seeking behavior will increase from baseline to 3 and 6 months by a greater amount in the Beyond Silence group than in the MHFA control. The primary approach to this question is the repeated measures analysis of a checklist of desirable help seeking/help providing behaviors, obtained from the survey at each time point. Overall tests of the change across all three measurements are available from generalized linear mixed-effects analysis, assuming that the count (from 0 to 20 behaviors) is distributed as a Poisson variable. This is a standard approach that accounts for over-dispersion in the Poisson model arising from the repeated measurements, permits the inclusion of participants who have not completed all three assessments, and allows for flexible modeling of the change over time and the inclusion of any relevant covariates [41]. In the primary analysis, the statistical significance of treatment group in this model will be used to address the first research question. In view of the randomized design, the primary analysis will not include additional covariates, but the model will be used to explore modifying effects by including additional covariates (e.g. age, sex, prior experience with mental illness) and interactions between these covariates and treatment group. As a secondary outcome, we will analyze a scaled measure of behavioral intentions using similar linear mixed-effects analysis.

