In Research Question 2, we propose mediating forces that are expected to be different in the two programs, including scaled measures of mental health literacy (expected to be higher in the MHFA group), stigma regarding mental illness (expected to be greater in the Beyond Silence group), and attitudes towards seeking professional help (expected to be higher in the Beyond Silence group). Following recommendations by Baron and Kenny [42], we will initially explore whether changes in literacy occur in association with the interventions. These analyses will use linear regression, modeling change in literacy and stigma, respectively, occurring in association with the interventions. Next, we will use Poisson or negative binomial regression to determine whether changes in literacy, stigma and attitudes associated with intervention (as well as overall levels of each) predict counts on the desirable behavior checklist. If associations are observed in both cases, we will evaluate change in these measures using linear mixed effects as described for Research Question 1. Substantial diminishment, or disappearance, of the effect of the interventions on help-seeking when the potential mediators are included in the model will be interpreted as providing evidence of mediation.

The random assignment of participants to intervention groups eliminates biases in the evaluation of the treatment effects, but the generalizability of this effect in relation to the representativeness of the sample will be assessed by comparing demographic and employment data from study participants to the equivalent data available for the entire organization. This data also provides insight on the reach of the program within the organization in terms of the characteristics of who volunteers to participate in this kind of program. This augments the qualitative analysis of Research Question 3.

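### The second step of the Research Question 2 mediation procedure admits overall mediator levels as predictors of the raw behavior count, so stable differences between people can satisfy it without any mediation

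*Protocol article*

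**What the plan says.** The Data analysis section of the protocol article sets out the mediation procedure for Research Question 2 in sequence.

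1. Linear regression, "modeling change in literacy and stigma, respectively, occurring in association with the interventions".
2. A count model (Poisson or negative binomial) with this purpose: "determine whether changes in literacy, stigma and attitudes associated with intervention (as well as overall levels of each) predict counts on the desirable behavior checklist".
3. A linking rule: "If associations are observed in both cases, we will evaluate change in these measures using linear mixed effects as described for Research Question 1".
4. A decision rule: a substantial fall in the program effect, or its loss, "when the potential mediators are included in the model will be interpreted as providing evidence of mediation".

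Three other statements bear on this. The Abstract describes the aim in terms of change: "Linear regression modeling will be used to explore the extent to which knowledge, and attitudes predict behavior change". For the Research Question 1 model, which step 3 reuses, "the primary analysis will not include additional covariates". In Data collection, the attitude scale (ATSPPHS) is described as having "criterion validity supported by links between scale scores and mental healthcare use".

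The article expects literacy to be higher under MHFA and attitudes to seeking help to be higher under Beyond Silence. It also expects stigma to differ in the direction of Beyond Silence, which I read as greater improvement.

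**The concern.** The mediation question is whether moving literacy, stigma or attitudes moves behavior. The matching null is that within-person change in the mediator has no bearing on change in behavior. A regression of the raw count on the mediator's overall level tests something else: whether people with better attitudes report more behaviors. A stable trait behind both makes that true without the mediator causing anything.

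Randomization protects the comparison of programs. It does not protect the mediator-to-behavior association, because nobody is randomized to a mediator value. An overall level that includes the post-program surveys also carries part of the program's shift. Putting it in the model can therefore take away part of the program effect for reasons unrelated to mechanism.

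At stake is the answer to Research Question 2. Attitude or stigma change could be credited as the mechanism of Beyond Silence when the data show only that people differ.

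**Working it through.** **Inputs from the article.** The trial is planned "with 100 participants in each group". The sample-size text in Participants gives variance 4, test-retest correlation 0.80, a baseline mean of about 1-2 behaviors (1.5 used) and a detectable difference of 0.44. Data collection gives test-retest reliability 0.66 for the stigma scale.

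**Inputs assumed, because the article gives none.** The program shifts the mediator by a = 0.3, 0.5 or 0.8 SD. The stable parts of mediator and behavior correlate at ρ = 0, 0.3 or 0.5. The causal effect of mediator on behavior is zero throughout.

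**The plan's own figure.** Detectable difference = (1.96 + 0.842) × √(2 × Var / 100).
- Mean of the two follow-ups minus baseline: Var = 1.5 × 4 × (1 − 0.80) = 1.2, giving 0.434.
- Simple baseline-to-6-month change: Var = 2 × 4 × (1 − 0.80) = 1.6, giving 0.501 two-sided or 0.445 one-sided.

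The stated 0.44 is reproduced under the first form, or the second one-sided. It is not in dispute and serves below as the program effect.

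**Step 2, count regression (600 trials per setting).** Baseline counts have mean 1.5 and variance 4. The way they were generated implies a test-retest correlation of 2.5/4 = 0.625, below the plan's 0.80. The 6-month count is regressed on program, mediator change and mean level, with robust standard errors.

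| ρ | level significant | change significant (level also in model) |
|---|---|---|
| 0 | 6-8% | 4-6% |
| 0.3 | 77-78% | 6-7% |
| 0.5 | over 99% | 6-8% |

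Step 1 passed in 72-100% of these trials, by design of the assumed shifts.

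**Final model, linear mixed form (1,000 trials per setting).** Variance is 4, correlation 0.80, with an uncentred time-varying mediator. The cross-sectional correlation between mediator and behavior is ρ × √(0.66 × 0.80) = 0.727ρ, so 0.22 at ρ = 0.3 and 0.36 at ρ = 0.5.

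| ρ | a (SD) | program-by-time effect, without → with mediator | fall |
|---|---|---|---|
| 0.3 | 0.3 | 0.441 → 0.407 | 8% |
| 0.3 | 0.5 | 0.433 → 0.374 | 14% |
| 0.3 | 0.8 | 0.434 → 0.342 | 21% |
| 0.5 | 0.3 | 0.442 → 0.383 | 13% |
| 0.5 | 0.5 | 0.438 → 0.340 | 22% |
| 0.5 | 0.8 | 0.446 → 0.290 | 35% |

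The fall equals b × a, where b is the fitted mediator coefficient: (0.438 − 0.340)/0.5 = 0.196, and (0.446 − 0.290)/0.8 = 0.195. The sign of a therefore sets the direction. With a = −0.5 at ρ = 0.5, as for a literacy score that favors MHFA, the effect would rise to 0.438 + 0.196 × 0.5 = 0.536.

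**How often mediation would be falsely declared.** A separate simulation used 400 trials per setting, negative binomial counts, mediator reliability 0.66 and zero mediation. The three rates in each row are for cross-sectional correlations of about 0.15, 0.24 and 0.32.

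| mediator shift | cutoff for a substantial fall | significant program effect required first | declared |
|---|---|---|---|
| 0.5 SD | 20% | no | 21 / 52 / 71% |
| 0.5 SD | 20% | yes | 9 / 23 / 38% |
| 0.5 SD | 30% | yes | 2 / 7 / 15% |
| 0.5 SD | 50% | yes | 0 / 0 / 1% |
| 0.3 SD | 20% | yes | 1 / 4 / 10% |
| 0.8 SD | 20% | yes | 23 / 47 / 57% |

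If only the change term can satisfy step 2, that step passes in 2-5% of trials. The 20% rule with a significant program effect then fires in at most 2%.

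**Check of the remedy.** With change in count regressed on change in mediator, adjusted for program, step 2 passes in 3-7% of trials and the program coefficient moves by −1% to +2%. With the mediator split into person mean and deviation, the deviation term is significant in 5-6% and the program-by-time effect stays at about 0.44.

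**The case against.** The main subject of the step 2 sentence is change. Levels appear in a parenthesis and can be read as accompanying terms rather than evidence. On that reading the step passes at close to the nominal rate. This stands as a possible reading, but the text does not say that a level association alone is insufficient.

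The form of the mediator in the final model is not stated. A reader might infer that it enters uncentred, so that shrinkage is built in. The article does not say so, and its reference to evaluating change could mean change only, where no shrinkage appears. The 8-35% is conditional on that choice.

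A reader might also infer from the validity statement for the attitude scale that level already predicts the outcome for every mediator. The statement covers that scale and mental healthcare use only, gives no size, and says nothing about stigma or literacy. The checklist also contains outreach behaviors.

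The deciding model does include the baseline count as one of its repeated measurements, so the lack of baseline adjustment concerns step 2 alone. Finally, the article treats this question as exploratory, warns in the Background that the relationships are complex, and adds qualitative data. The primary comparison is untouched. That limits the weight of the point but does not remove it.

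**Conclusion.** The point holds in conditional form. As worded, step 2 lets mediator level predict the raw count. If that association counts, a stable trait alone satisfies the step in about 77% of trials at ρ = 0.3 and over 99% at ρ = 0.5, while the change term stays near 5%. Step 1 must still show a program difference in mediator change. If levels or an uncentred mediator reach the final model, the program effect falls by about 8-35% over the assumed range for mediators favoring Beyond Silence, and grows for a literacy difference favoring MHFA.

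A reader might conclude that the plan would falsely declare mediation in most trials, or whenever a program shifts a scale. The article does not support that. The rate depends on an undefined cutoff, an unknown mediator shift and whether a program effect must first be detected, and runs from near 0% to over half of trials. The mediator shifts and trait correlations are assumptions throughout. The consequence is confined to Research Question 2, whose mediation conclusion would be hard to trust as specified.

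**What to change.** In Data analysis, under Research Question 2:

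- Do not count the parenthesis on overall levels as evidence for the second step.
- Test whether within-person change in each mediator predicts change in the behavior count, adjusted for program.
- In the final mixed model, split each mediator into the person's mean and the deviation from it. Base any mediation statement on the deviation term, and report level associations as descriptive.
- Acknowledge that time-varying confounding of mediator and behavior remains.

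This changes wording and analysis only, because all three surveys already collect the mediators and the behaviors. The cost is some precision on the mediator-to-behavior path, since between-person information is no longer used there.

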## Abstract

**Background:**

Mental illness is a significant and growing problem in Canadian healthcare organizations, leading to tremendous personal, social and financial costs for individuals, their colleagues, their employers and their patients. Early and appropriate intervention is needed, but unfortunately, few workers get the help that they need in a timely way due to barriers related to poor mental health literacy, stigma, and inadequate access to mental health services. Workplace education and training is one promising approach to early identification and support for workers who are struggling. Little is known, however, about what approach is most effective, particularly in the context of healthcare work. The purpose of this study is to compare the impact of a customized, contact-based education approach with standard mental health literacy training on the mental health knowledge, stigmatized beliefs and help-seeking/help-outreach behaviors of healthcare employees.

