**Figure 1 Fig1:**
[figure not shown]
Conceptual Model of Early Intervention.

As outlined in the conceptual model, there are several key forces that may shape the nature and extent of early intervention for mental health problems. Mental health literacy, stigma, and beliefs about the value of seeking help are some of the key forces to consider [18]. Mental health literacy refers to the knowledge and skills required for recognition, management and/or prevention of mental disorders [19,20]. Literacy is a critical issue because many mental health problems are misunderstood or over-looked, therefore early identification is the first critical step in early intervention. Stigma, in the form of negative attitudes and stereotypical beliefs about mental illness is another key issue. Co-workers often judge workers with a mental illness and ostracize them rather than provide support [21]. These attitudes and beliefs contribute to fear of discrimination and are a substantial barrier to seeking help [22]. Another force that may shape behavior is one’s belief about the role and effectiveness of psychological treatment. If there is little faith in the value of a treatment approach, then a worker may not choose to pursue the treatment, and likewise a colleague may not recommend it to a co-worker who is struggling [18].

It should be noted that the model depicts a linear relationship between the key variables, however these relationships can be quite complex, and not always predictable. For example, mental health literacy training may or may not affect stigmatized beliefs; a decrease in stigma may not affect behavior; and experience in seeking help may reinforce or change beliefs about the value of a particular approach [23].

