Compliance with the programs will be tracked through attendance rates, with 75% attendance considered to be good compliance. To minimize withdrawals or missing data, multiple strategies will be put in place to allow participants to respond (written, electronic) with incentives for survey completion and proactive follow-up by email and/or phone. Based on the level of engagement of pilot participants, minimal loss to follow-up is expected, but we will impute assuming random missing-ness if needed. The repeated measures mixed effects model accounts for missing data under a missing at random assumption, such that participants with a single missing follow-up survey do not need to be excluded from the data analysis.

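### The three-survey mixed model for literacy and stigma is fitted only if both mediation associations appear, although one of them has no bearing on whether the programs differ on those scales

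*Protocol article*

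**What the plan says.** The Abstract (Background) gives the purpose as comparing the two programs "on the mental health knowledge, stigmatized beliefs and help-seeking/help-outreach behaviors of healthcare employees". The Research questions section places literacy and attitudes under the mediation question, and the Background names behavior as the primary outcome.

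For Research Question 2, the Data analysis section sets out a sequence:

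1. Program and scale: "These analyses will use linear regression, modeling change in literacy and stigma, respectively, occurring in association with the interventions". No condition is attached.
2. Scale and behavior: Poisson or negative binomial regression is used to see whether "changes in literacy, stigma and attitudes associated with intervention (as well as overall levels of each) predict counts on the desirable behavior checklist".
3. Repeated measures: "If associations are observed in both cases, we will evaluate change in these measures using linear mixed effects as described for Research Question 1".
4. Mediation is then judged by how far the program effect on behavior shrinks once the mediators enter the model.

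Three other statements bear on this. The conceptual-model text under Figure 1 warns that "a decrease in stigma may not affect behavior". The missing-data paragraph under Participants says of the mixed model that "participants with a single missing follow-up survey do not need to be excluded from the data analysis", and also allows imputation. The Research Question 1 paragraph gives behavioral intentions a linear mixed model with no condition.

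**The concern.** Whether two randomized programs differ in their effect on stigma or literacy can be answered from the randomization alone. It does not depend on whether the scale goes on to predict behavior. Step 3 nevertheless makes the three-survey analysis of these scales wait for that second association.

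For stigma, the article itself foresees that this association may be absent. If Beyond Silence lowers stigma and behavior does not move, the rule as written means that the mixed model of stigma is not fitted. Behavioral intentions, also secondary, face no such rule, and no reason is given for the difference.

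At stake is the quality of the evidence on two scales named in the purpose. The model that combines both follow-up surveys, and handles a missed survey under missing at random, would be available only in trials that passed both steps. Estimates from it would then be selected estimates.

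**Working it through.** **The plan's own figure.** The article gives no effect size or power for literacy or stigma. Its one precision figure is 0.44 behaviors, from 100 per group, variance 4, correlation 0.80, 80% power and p < .05. Taking the mean of the two follow-ups minus baseline under equal correlations, the variance is 4 × (1 − 0.80) × 1.5 = 1.2. The detectable difference is (1.96 + 0.84) × √(2 × 1.2/100) = 0.434, close to 0.44. A simple two-point change (variance 4 × 0.20 × 2 = 1.6) gives 0.501 two-sided. The figure does not enter the argument below.

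**What each step conditions on**

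| Analysis | Condition | Bears on whether the programs differ on the scale? |
|---|---|---|
| Regression of change in literacy and stigma | none | yes |
| Mixed model, all three surveys | program associated with scale change | yes, but it selects on the result |
| Mixed model, all three surveys | scale predicts behavior | no |

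**How often the mixed model would be reached.** The article sets no threshold, so a 5% test for each association is assumed. With the stigma scale's reliability of 0.66, the variance of a two-point change is 2 × (1 − 0.66) = 0.68 in SD units. The effect detectable with 80% power at 100 per group is (1.96 + 0.84) × √(2 × 0.68/100) = 0.33 SD. Taking the two tests as independent, the probability of reaching the mixed model is the product of the two powers:

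- stigma change does not affect behavior: 0.80 × 0.05 = 4%
- second association has 30% power: 0.80 × 0.30 = 24%
- 50% power: 0.80 × 0.50 = 40%
- 80% power: 0.80 × 0.80 = 64%

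A simulation of 1,000 trials per setting assumed a baseline mean of 1.5 behaviors, log-normal over-dispersion with SD 0.7, and Poisson regression with robust standard errors. It gave 5.2% with no stigma–behavior link. With log-rate slopes of 0.1, 0.2 and 0.3 per SD of stigma change it gave 19.8%, 59.2% and 76.6%. The program–stigma association was found in about 80% of trials throughout.

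**Selection of the gated estimate.** For an estimate reported only when z > 1.96, with true z = 1.96 + Φ⁻¹(power), the expected z given significance is z + φ(1.96 − z)/(1 − Φ(1.96 − z)).

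| Power | True z | Expected z if significant | Ratio |
|---|---|---|---|
| 30% | 1.44 | 2.59 | 1.81 |
| 50% | 1.96 | 2.76 | 1.41 |
| 80% | 2.80 | 3.15 | 1.12 |

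These ratios illustrate selection on the first condition only. They assume the 5% threshold, and that the tested and reported estimates are essentially the same quantity.

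**The case against.** The strongest reply is that the randomized comparison is always made. Step 1 regresses change in literacy and stigma on program with no condition. A reader might infer that the knowledge and stigma question is answered only through a filter; the text does not support that. If the first regression and the mixed model estimate nearly the same quantity, an unselected estimate exists in every scenario, and the inflation ratios describe only the gated one. This stands.

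A reader might also infer that the change regression contradicts the missing-data paragraph, or must be complete-case. Neither follows. The sentence about a single missed survey describes the mixed model, not every analysis. The same paragraph provides for imputation if needed and expects little loss to follow-up. This also stands.

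Third, the condition sits inside a Baron and Kenny sequence, where requiring both paths before judging mediation is ordinary. That is a fair reading of its origin. Even so, no other sentence gives literacy or stigma an unconditional repeated-measures analysis, so the purpose stated in the Abstract still lacks one.

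Three narrower replies are right. No p-value threshold is stated, so a significance filter is an inference. The warning about behavior under Figure 1 concerns stigma and says nothing similar about literacy. The attitudes scale may be the behavioral-intentions measure that already has an unconditional mixed model. Finally, the article calls precision for the mediators similarly high; if so, the 80% row, an overstatement of about 12%, is the relevant one.

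**Conclusion.** The point holds in a limited form. The mixed model of the mediator scales depends on two associations, and the one between scale and behavior is irrelevant to whether the programs differ on literacy or stigma. The comparison is weakened rather than lost: the unconditional regression remains, while the analysis using both follow-ups and partly observed participants is run only after selection.

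Under the assumed 5% tests and 80% power for a real stigma effect, that analysis would be reached about 4% to 5% of the time if stigma change does not affect behavior, and 24% to 64% of the time for 30% to 80% power on the second association. These are illustrations, since the article gives neither an effect size for these scales nor a threshold. The matter concerns secondary analyses and leaves the primary result untouched. It merits a change because the change costs almost nothing.

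**What to change.** Remove the condition from the repeated-measures analysis of the scales. State that a linear mixed model with program-by-survey terms will be fitted to literacy and to stigma for all randomized participants, whatever the mediation steps show. Do the same for the attitudes scale unless it is already the behavioral-intentions measure analyzed under Research Question 1, and say which it is. Report the group difference in change at the post-program and 3-month follow-up surveys with confidence intervals. Keep any requirement for both associations for the mediation step only.

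The cost is a sentence of text and two or three routine model fits, with no new data and no change to the sample size or the primary analysis.
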